##### Behavioral measures of cognitive control

2.3.3.5

Given the central role of the dACC in cognitive control, participants will complete the Go/No-Go and Stroop color–word tasks. Response inhibition will be evaluated with the Go/No-Go paradigm, in which participants are required to respond promptly to Go stimuli while withholding responses to No-Go stimuli (42). The derived indices will comprise overall accuracy, Go and No-Go accuracy, omission and commission error rates, reaction time for correct Go trials, and *d*′. The Stroop color–word task will be administered to characterize conflict processing and cognitive control. Participants will identify the font color of each stimulus while disregarding the meaning of the displayed word (43). The analysis will include overall and condition-specific accuracy, reaction times for congruent and incongruent trials, and the Stroop interference effect.

##### Neuroimaging outcomes

2.3.3.6

MRI data will be acquired on a 3.0-T uMR 780 scanner (United Imaging Healthcare, Shanghai, China). Exploratory analyses will include rs-fMRI and DTI measures.

DTI will be collected with 64 diffusion directions and b-values of 0 and 1000 s/mm². Whole-brain coverage will be obtained with 64 interleaved slices at 2.5-mm isotropic resolution. The sequence parameters will be TR = 10,232 ms, TE = 69.7 ms, flip angle = 90°, field of view = 220 × 220 mm², and anterior-to-posterior phase encoding. For rs-fMRI, echo-planar images will be acquired with 37 interleaved slices and a voxel size of 3 × 3 × 3.5 mm³. The sequence will use TR = 2000 ms, TE = 30 ms, flip angle = 90°, field of view = 216 × 216 mm², and posterior-to-anterior phase encoding. Other assessments and covariates.

Baseline data collection will cover demographic characteristics, clinical history, and lifestyle-related factors. Demographic variables will include age, sex, marital status, educational attainment, employment status, and income level. Clinical information will include illness duration, age at onset, previous hospitalizations, treatment history, and the type and dosage of current antipsychotic medication. Smoking status, alcohol consumption, and other potentially relevant lifestyle factors will also be recorded. Antipsychotic doses will be converted into daily chlorpromazine-equivalent doses using the international consensus method proposed by Gardner et al. For participants receiving more than one antipsychotic medication, the chlorpromazine-equivalent dose of each agent will be calculated separately and then summed to obtain the total daily chlorpromazine-equivalent dose. These values will be summarized descriptively and, when prespecified, incorporated into covariate-adjusted analyses.

Participants’ perceptions of the credibility of tTIS and their expectations regarding treatment benefit will be measured at baseline with an adapted version of the Credibility/Expectancy Questionnaire (CEQ) (44). CEQ scores will be considered as potential covariates in sensitivity analyses.

### Safety assessments

2.4

The incidence and severity of adverse events will be assessed throughout the study period, from baseline to the 4-week follow-up. Treatment tolerability and adherence will also be documented during the intervention period. Detailed procedures for adverse event monitoring and reporting are described in the section on oversight and monitoring.

### Sample size

2.5

Sample size was estimated using a Monte Carlo simulation–based power analysis for a mixed-effects model for repeated measures (MMRM). Based on findings from previous meta-analyses of non-invasive brain stimulation for negative symptoms in schizophrenia, the anticipated standardized between-group effect size at T1 was set at Cohen’s (d=0.60) (45). To account for a possible partial attenuation of the treatment effect during follow-up, the effect size at T2 was conservatively set at (d=0.40).

The correlations between baseline and T1, baseline and T2, and T1 and T2 assessments were assumed to be 0.50, 0.40, and 0.60, respectively. The cumulative rates of missing outcome data were assumed to be 5% at T1 and 10% at T2. The MMRM used in the simulations included treatment group, visit, the treatment group-by-visit interaction, baseline PANSS-NS score, and the baseline score-by-visit interaction as fixed effects. An unstructured covariance matrix, restricted maximum likelihood estimation, and the Kenward–Roger approximation were applied.

Simulations were conducted in R version 4.6.1 using the MASS, mmrm version 0.3.18, and emmeans version 2.0.4 packages. For each candidate sample size, 10,000 simulated trials were generated. Statistical power was defined as the proportion of simulations in which the two-sided (P) value for the primary between-group comparison at T1 was less than 0.05. The estimated power was 79.86% with 36 participants per group and 80.77% with 37 participants per group. Therefore, the planned sample size is 74 participants, with 37 participants allocated to each group.

### Assignment of interventions

2.6

#### Sequence generation

2.6.1

Randomization will take place after the baseline evaluation has been completed and eligibility has been confirmed. Participants will enter either the active tTIS arm or the sham arm with equal probability. The allocation list will be created in IBM SPSS Statistics version 25.0 using a simple randomization procedure. This task will be undertaken by a researcher whose responsibilities are restricted to randomization management and who will take no part in recruitment, eligibility screening, stimulation delivery, outcome evaluation, or data analysis.

#### Allocation concealment

2.6.2

Group assignments will be concealed in consecutively numbered, non-transparent, sealed envelopes with the same external appearance. The envelopes will be assembled and retained by the researcher responsible for randomization management. Once a participant has completed the baseline evaluation and enrollment procedures, the intervention operator will open the next available envelope immediately before treatment allocation is implemented. The allocation list will remain unavailable to outcome assessors and to research personnel who do not require access for intervention delivery.

#### Blinding

2.6.3

Participants and outcome assessors will be blinded to treatment allocation. The active and sham stimulation procedures will follow the same schedule and use identical electrode placement procedures. The sham stimulation procedure will include ramp-up and ramp-down phases to mimic the sensory experience of active stimulation. Because the intervention parameters must be configured according to group allocation, the staff member responsible for delivering the stimulation cannot be blinded. This staff member will also be responsible for safety monitoring and adverse-event assessments during the intervention period, but will not participate in participant recruitment, clinical or cognitive assessments, data management, or statistical analysis. Safety and adverse-event information will be recorded separately and will not be disclosed to the blinded outcome assessors. Interactions between the intervention staff and participants will be limited to those necessary for stimulation delivery and safety monitoring.

The researchers responsible for data analysis will remain blinded to group allocation until the primary analyses have been completed. Group labels will be coded using neutral identifiers, such as Group A and Group B. The allocation code will be revealed only after the statistical analysis plan has been finalized and the main analyses have been completed.

After the intervention, participants and outcome assessors will be asked to guess the assigned treatment group and indicate the basis for their judgment.

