Interventional evidence suggests that the prefrontal–cingulate–striatal network may have therapeutic value in schizophrenia. Stimulation of the prefrontal cortex using TMS has shown potential benefits for both cognitive deficits and negative symptoms (20). Preliminary findings from deep TMS studies indicate that modulation of the anterior cingulate cortex is well tolerated and may alleviate the overall severity of psychotic symptoms (21). Neuroimaging studies of pharmacological treatment offer converging support for the involvement of this network. Cognitive improvement has been linked to stronger coupling of the dorsolateral prefrontal cortex with the anterior and mid-cingulate regions (22), whereas symptomatic improvement has been related to enhanced connectivity across the striatum, anterior cingulate cortex, and dorsolateral prefrontal cortex (23). Collectively, these observations provide a rationale for evaluating the dACC as a candidate target for neuromodulation in schizophrenia.

Accordingly, we designed a randomized, participant- and outcome-assessor-blinded, sham-controlled trial to evaluate dACC-targeted tTIS in individuals with schizophrenia. The primary objective is to determine whether active stimulation reduces negative symptom severity compared with sham stimulation. Secondary objectives are to examine changes in cognitive performance, broader clinical outcomes, behavioral indices of cognitive control, safety, tolerability, and multimodal neuroimaging measures. The findings may inform the development of more targeted and individualized neuromodulation strategies for schizophrenia.

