Study records will be handled in accordance with the purposes of the trial. Upon enrollment, each participant will be identified by a study-specific code. Information that could reveal the identity of an individual participant will be maintained separately from the analysis dataset and will not appear in research reports, conference materials, or publications. Data will initially be recorded on paper case report forms (CRFs). Two data managers will independently transfer the information into a password-protected electronic database. The two electronic records will then be compared. Where inconsistencies are identified, the original CRFs will be reviewed, with source documents consulted when clarification is required.

Before enrollment commences, all personnel involved in the study will complete protocol-specific training appropriate to their responsibilities. Clinical assessors will be trained in the consistent administration of symptom ratings and cognitive measures, while intervention operators will receive instruction in the standardized delivery of tTIS and the recording of adverse events. MRI technicians will be briefed on the acquisition protocol and image-quality requirements. Training will also address participant communication and the accurate completion of study documentation.

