#### Adverse event reporting and harms

2.10.2

Every AE occurring from enrollment through the end of the follow-up period will be prospectively recorded in CRFs, with documentation encompassing event description, date of onset, duration, severity, therapeutic measures taken, clinical outcome, and the assigned investigator’s assessment of its relationship to tTIS. A designated study physician will adjudicate potential attribution to the intervention for each event. Non-serious AEs will receive clinically appropriate management and be tracked until full resolution or stabilization. Any SAE must be reported to the principal investigator within 24 hours of the research team becoming aware, and subsequently notified to the Ethics Committee in accordance with institutional and regulatory obligations. AEs judged as possibly or probably related to tTIS will be escalated to the DSMB, which will deliberate on whether additional safety measures, protocol modifications, temporary recruitment suspension, or premature trial closure are warranted.

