This study also has several limitations. First, because of the operational characteristics of the current tTIS device, the staff responsible for intervention delivery cannot be blinded to treatment allocation. To reduce the risk of performance bias, intervention delivery, outcome assessment, and statistical analysis will be performed by separate personnel. Outcome assessors and data analysts will remain blinded, and interactions between intervention staff and participants will be limited to those required for treatment delivery (25). Second, differences in scalp sensations may affect the effectiveness of the sham procedure. Although brief ramp-up and ramp-down phases will be used to mimic the sensory experience of active stimulation, this approach may not completely mask group allocation in all participants (47). Treatment expectancy will therefore be assessed at baseline, and blinding success will be evaluated after the intervention. Third, the 10-session intervention period and the 4-week follow-up are relatively short for evaluating changes in negative symptoms. The study may therefore underestimate the longer-term therapeutic potential of dACC-targeted tTIS. Fourth, the exploratory nature of this single-center study and its modest sample size limit the broader applicability of the findings. Larger multicenter trials with longer treatment courses and extended follow-up periods will be required to evaluate the durability and generalizability of the observed effects. The neuroimaging analyses are also exploratory and may be influenced by antipsychotic dose, illness duration, baseline symptom severity, and individual variability (48).

This study will generate initial evidence regarding the clinical relevance of dACC-focused tTIS for schizophrenia and its associated neurobiological changes. The integration of symptom ratings, cognitive measures, behavioral performance, and multimodal imaging may help clarify whether modulation of this circuit is feasible and therapeutically promising. The results will provide a foundation for subsequent multicenter studies with larger samples and may contribute to the refinement of individualized, circuit-informed neuromodulation approaches for schizophrenia.

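### The unblinded stimulation operator assesses adverse events during treatment, so the active-versus-sham safety comparison is open to ascertainment and grading bias

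*Protocol article*

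**What the plan says.** Blinding (2.6.3) explains that parameters are set according to allocation, so "the staff member responsible for delivering the stimulation cannot be blinded". It then gives that person a second role: "This staff member will also be responsible for safety monitoring and adverse-event assessments during the intervention period". Data collection and management (2.7) agrees: "intervention operators will receive instruction in the standardized delivery of tTIS and the recording of adverse events".

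The same Blinding section states "Participants and outcome assessors will be blinded to treatment allocation", and adds the data analysts. It names no blinded person who elicits or grades adverse events. It also walls the safety data off: "Safety and adverse-event information will be recorded separately and will not be disclosed to the blinded outcome assessors".

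Safety is a declared target of the trial. The secondary objectives at the end of the Introduction include "behavioral indices of cognitive control, safety, tolerability, and multimodal neuroimaging measures". Table 1 places the safety, tolerability and adverse-event row in its outcome-assessment block. Safety analysis (2.8.6) reports events by allocated arm, with severity grade and causal relationship.

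Adverse event reporting and harms (2.10.2) gives attribution of each event to a designated study physician and adds: "AEs judged as possibly or probably related to tTIS will be escalated to the DSMB".

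The Discussion, addressing the unblinded operator as a limitation, says that "intervention delivery, outcome assessment, and statistical analysis will be performed by separate personnel".

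**The concern.** Most tolerability events with scalp stimulation are subjective: discomfort, headache, dizziness, skin sensation. Whether one is recorded, and at what grade, depends on how the participant is asked and how the answer is judged. Someone who knows the arm may probe harder or grade higher under active stimulation, or may play down complaints there. Either way the difference between arms then mixes true effect with recording behaviour.

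The section on active stimulation (2.2.2) concedes that direct evidence for ten sessions at the maximum permitted intensity is limited. The active-versus-sham tolerability profile is thus one of the more useful things this trial can deliver, and an event that was never elicited cannot be recovered later. The Discussion treats the unblinded operator only as a performance-bias risk, so a reader of the results would not be warned.

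**Working it through.** **Plan's own figure.** The document gives no adverse-event rate, so there is none to reproduce. Its only design figure is power for the primary contrast, 80.77% with 37 per arm. A simulated baseline-adjusted analysis with 5% missing at T1 gives 80.9%, so that figure stands. It has no bearing here beyond supplying n = 37 per arm.

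**Step 1: does the separation cover safety?**

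| Question | Clinical and cognitive outcomes | Safety, Weeks 1–2 |
|---|---|---|
| Declared objective? | Yes (Introduction) | Yes (Introduction) |
| In the outcome block of Table 1? | Yes | Yes |
| Who assesses? | Blinded assessors (2.6.3) | The unblinded operator (2.6.3) |
| Separate from delivery? | Yes | No |
| Reported by arm? | Yes (2.8) | Yes, with severity and causality (2.8.6) |

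The separation statement is true of the first column and not of the second.

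**Step 2: is there a blinded person downstream?** The study physician in 2.10.2 adjudicates attribution. The physician is in none of the groups that 2.6.3 lists as blinded. For events in the treatment weeks the source is the operator's record. Physician review can correct a biased attribution, but not an event that was missed. No one other than the operator is named as grading severity in this period.

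**Step 3: how sensitive is the comparison?** Four participants recorded in one arm who would not have been recorded under blinded assessment change that arm's rate by 4/37 = 0.108, or 10.8 percentage points.

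**Step 4: differential recording (assumed values).** Let the true proportion with an event be p in both arms, and let an event be recorded with probability r_A (active) and r_S (sham). Then:

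- recorded proportions are p·r_A and p·r_S;
- spurious risk difference = p(r_A − r_S);
- spurious risk ratio = r_A / r_S, whatever p is.

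With r_A = 0.9:

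| r_S | Risk ratio | Difference, p = 0.2 | p = 0.4 | p = 0.6 |
|---|---|---|---|---|
| 0.8 | 0.9/0.8 = 1.125 | 2 points | 4 points | 6 points |
| 0.7 | 0.9/0.7 = 1.29 | 4 points | 8 points | 12 points |
| 0.6 | 0.9/0.6 = 1.50 | 6 points | 12 points | 18 points |

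Example: at p = 0.4 and r_S = 0.7, expected counts are 37 × 0.36 = 13.3 and 37 × 0.28 = 10.4 with no true difference. If the operator under-records in the active arm, the signs reverse. These inputs are assumptions; they show what is possible and do not estimate what will happen.

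**The case against.** The strongest defence has four parts.

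- **The arrangement is disclosed and partly deliberate.** Someone must watch the participant during stimulation, and keeping safety data from the efficacy raters protects their blinding. This stands. It justifies the operator's monitoring role, but not making that person the source for a between-arm comparison when the participant is blinded and can report directly.
- **The Discussion sentence is about performance bias.** Safety assessments (2.4) also sits outside Outcomes (2.3). Read narrowly, the sentence agrees with 2.6.3, so this is a matter of scope and nothing is hidden. But Table 1 and the objectives treat safety as an outcome, so the sentence needs limiting.
- **Safety is descriptive, with no test.** True, and it lowers the stakes. Descriptive rates by arm will still be read as a comparison.
- **An article may leave the checklist to the full protocol.** Fair; the absence of a form is not the point. The assignment of assessment to the unblinded operator is stated.

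Three stronger readings are tempting, and the document does not support them.

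- A reader might infer that the operator decides relatedness and will rarely call a sham event related. Attribution belongs to the study physician (2.10.2). Allocation concealment (2.6.2) withholds the list from staff who do not need it for delivery, which appears to include that physician. Sham also delivers ramp currents (2.2.3), so a sham event can plausibly be judged related.
- A reader might infer that the DSMB sees only events filtered by attribution. Section 2.10.1 has it review serious and non-serious events at its meetings; the relatedness-based escalation is an additional route.
- A reader might infer that the efficacy result is compromised. The operator takes no part in clinical or cognitive assessment, and safety data are kept from the raters.

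**Conclusion.** The concern holds for safety and tolerability in the two treatment weeks. Following the plan as written leaves the active-versus-sham comparison open to ascertainment and grading bias, and the Discussion's separation statement does not extend to these outcomes. Bias in attribution is not shown; what is missing is a statement that the adjudicating physician is blind, together with a record that does not come only from the operator.

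Direction and size are unknown. The illustrative range (risk ratio 1.125 to 1.5, difference 2 to 18 points) rests wholly on the assumed event risks and recording probabilities. The operator's assessment role is stated only for the intervention period, so later events are not shown to be affected. The PANSS-NS, BACS and SANS analyses are untouched. This is a worthwhile, inexpensive improvement and not a threat to the trial's main conclusion.

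**What to change.** 1. Have the blinded participant complete the same fixed symptom checklist, with the same grading, before and after every session in both arms.
2. Have the already planned study physician grade severity and relatedness from those forms, and state that this physician is blind to allocation.
3. Keep the operator for immediate safety monitoring and for recording acute events, and mark operator-recorded events as such in the data.
4. Limit the Discussion's separation statement to the clinical and cognitive outcomes. List operator-recorded adverse events as a limitation, including for participants already treated: Trial status gives enrollment as open since June 30, 2026, and their records cannot be collected again.

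No change to DSMB routing is needed for this point.

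Cost: one form, a wording change, and a few minutes per session; no new staff. More minor symptoms will be recorded in both arms, so rates before and after the change should not be pooled without saying so.

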### Data collection and management

2.7

Outcome evaluations will be completed at T0, T1, and T2. **Table 1** provides a detailed overview of participant enrollment, treatment delivery, and data collection across the study period.

**Table 1 T1:** SPIRIT schedule of enrollment, interventions, and assessments.

Study phase/assessment	Screening	Baseline and randomization (T0)	Intervention period (Weeks 1–2)	Post-intervention (T1)	4-week follow-up (T2)
Enrolment and allocation					
Eligibility screening	x				
Informed consent	x				
Demographic and clinical characteristics		x			
Randomization		x			
CEQ		x			
Interventions					
Active TI stimulation			10 sessions, 30 min/session		
Sham stimulation			10 sessions, 30 min/session		
Outcome assessments					
PANSS-NS		x		x	X
BACS composite *z* score		x		x	X
SANS score		x		x	X
Other secondary clinical outcomes^a^		x		x	X
Go/No-Go and Stroop tasks		x		x	X
Structural MRI (T1-weighted)		x			
rs-fMRI and DTI		x		x	X
Safety, tolerability, treatment adherence, and adverse events		x	x	x	X

BACS, Brief Assessment of Cognition in Schizophrenia; CEQ, Credibility/Expectancy Questionnaire; DTI, diffusion tensor imaging; PANSS, Positive and Negative Syndrome Scale; PANSS-NS, PANSS negative symptom subscale; rs-fMRI, resting-state functional magnetic resonance imaging; TI, temporal interference stimulation.

^a^Other secondary clinical outcomes include PANSS total, positive symptom subscale, and general psychopathology subscale scores; self-rated Apathy Evaluation Scale (AES-S); Temporal Experience of Pleasure Scale (TEPS); Personal and Social Performance Scale (PSP); World Health Organization Quality of Life-BREF (WHOQOL-BREF); Pittsburgh Sleep Quality Index (PSQI); Patient Health Questionnaire-9 (PHQ-9); and Generalized Anxiety Disorder-7 (GAD-7).

Study records will be handled in accordance with the purposes of the trial. Upon enrollment, each participant will be identified by a study-specific code. Information that could reveal the identity of an individual participant will be maintained separately from the analysis dataset and will not appear in research reports, conference materials, or publications. Data will initially be recorded on paper case report forms (CRFs). Two data managers will independently transfer the information into a password-protected electronic database. The two electronic records will then be compared. Where inconsistencies are identified, the original CRFs will be reviewed, with source documents consulted when clarification is required.

Before enrollment commences, all personnel involved in the study will complete protocol-specific training appropriate to their responsibilities. Clinical assessors will be trained in the consistent administration of symptom ratings and cognitive measures, while intervention operators will receive instruction in the standardized delivery of tTIS and the recording of adverse events. MRI technicians will be briefed on the acquisition protocol and image-quality requirements. Training will also address participant communication and the accurate completion of study documentation.

